#### Level 2 of diagnostic certainty

Newborn infant weighed within 24 h of birth

AND

Scale (electronic/spring) is graduated to at least 50 g

AND

Scale is calibrated at least once a year, or more often if moved

AND

Scale tared to zero grams or 0.00 kg

AND

Weight recorded as <2500 g

OR

Birth weight recorded as <2500 g

AND

Birth weight assessed as per health care facility's standard operating procedure, which fulfills criteria 1 to 4 of LOC2

Scale used: could be electronic or spring scale, including color-coded scale.

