### Level 1 of diagnostic certainty

- Weight below 10th percentile for gestational age  
AND

---

 The case definition should be applied when there is no clear alternative diagnosis for the reported event to account for the combination of symptoms.

- The following used in assessment of weight:
  - o Newborn weighed within 24 h of birth
  - o Weight assessed using a calibrated electronic scale with 10 g resolution
 AND
- The following for assessment of gestational age:
  - o Certain LMP or IUI or embryo transfer date AND confirmatory ultrasound in first trimester
 OR
  - o First trimester ultrasound

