#### Level 2A of diagnostic certainty

- Weight below 10th percentile for gestational age
- AND
- The following used in assessment of weight
  - o Newborn weighed within 24 h of birth on any scale with a <50 g resolution, tared to zero and calibrated
 AND
- The following for assessment of gestational age:
  - o Certain LMP with first or second trimester ultrasound
 OR
  - o Certain LMP with first trimester physical exam^3

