#### Level 3A of diagnostic certainty

- Weight below 10th percentile for gestational age
- AND
- The following used in assessment of weight
  - o Infant weighed within the first 48 h of life
  - o Newborn weighed on any scale with a <50 g resolution, tared to zero and calibrated
 AND

---

 If Physical exam and ultrasound do not correlate, default to ultrasound.

- The following assessment of gestational age
  - o Certain LMP with third trimester ultrasound
  - OR
  - o Certain LMP with confirmatory 2nd trimester fundal height
  - OR
  - o Certain LMP with birthweight
  - OR
  - o Uncertain LMP with first trimester physical exam

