#### Level 3B of diagnostic certainty

- Weight below 10th percentile for gestational age
- AND
- The following used in assessment of weight
  - o Infant weighed within the first 48 h of life
  - o Newborn weight assessed by measuring the difference between an adult holding the infant and the adult being weighed alone on any scale
- AND
- The following assessment of gestational age
  - o Uncertain LMP with fundal height
  - OR
  - o Uncertain LMP with newborn physical assessment
  - OR
  - o Uncertain LMP with birthweight

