#### Level 4 of diagnostic certainty

- Baby noted to be small, but no actual weight
- Baby with GA assessed only by infant examination
- Diagnosis extracted from billing codes or chart, with no documentation of actual birth weight or GA

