| Scale |                                                                                       |                                                                                                    |
| 1            | What type of scale was used?                                                          | Electronic scale
Spring scale
Dial
Color-coded
Unknown                                 |
| 2            | How is the scale graduated?                                                           | To 10 grams
To at least 50 grams
Other
Unknown                                            |
| 3            | How often is the scale calibrated?                                                    | At least once a year
At least once a year, or more often if moved
Other
Unknown           |
| 4            | What is the scale tared to?                                                           | 0 grams
0.00 kg
Other
Unknown                                                             |
| 5            | (For electronic scales): Is the scale placed on a level, hard surface?                | Yes
No
Unknown                                                                               |

|                                                                           |                                                                                                                                                                                                                                                                       |                      |
|---------------------------------------------------------------------------|-----------------------------------------------------------------------------------------------------------------------------------------------------------------------------------------------------------------------------------------------------------------------|----------------------|
| 6                                                                         | Is the infant weighed by measuring the difference between an adult holding the infant and the adult being weighed alone?                                                                                                                                              | Yes
No
Unknown |

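### The birth-weight form's 50 g answer cannot decide the SGA scale criterion, so at sites whose scale is not graduated to 10 g some SGA cases are classified or not by how that answer is mapped

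*Protocol*

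**What the plan says.** In Protocol Annex V, Reference CRF: birth weight, Scale item 2 asks how the scale is graduated and lists four answers: "To 10 grams To at least 50 grams Other Unknown". The answer at issue is the second, "To at least 50 grams". Other carries no free text, and no numeric graduation is collected. The SGA form in the same annex has no weight items of its own and refers to this reference form.

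Annex III sets the scale criteria:

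- Low birth weight (LBW) Level 1 needs an electronic scale graduated to 10 g. Level 2 says "Scale (electronic/spring) is graduated to at least 50 g". Both levels can also be met through the facility's standard operating procedure (SOP), which is asked once per site.
- SGA Level 1: "Weight assessed using a calibrated electronic scale with 10 g resolution".
- SGA Levels 2A and 2B: "Newborn weighed within 24 h of birth on any scale with a <50 g resolution, tared to zero and calibrated".
- SGA Level 3A: "Newborn weighed on any scale with a <50 g resolution, tared to zero and calibrated".
- SGA Level 3B: "Newborn weight assessed by measuring the difference between an adult holding the infant and the adult being weighed alone on any scale".

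Section 4.10 has cases classified by an automatic tool. Section 5.2.2.1 makes the number of classified cases the numerator of applicability, reported overall and by site. Section 5.5 analyses the data as recorded in the eCRFs, without imputation.

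**The concern.** The two graduation answers are the LBW Level 1 and Level 2 limits. SGA draws the line elsewhere: LBW Level 2 admits a 50 g scale, and SGA Levels 2A, 2B and 3A exclude it. An item built for the first limit cannot decide the second.

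Graduation belongs to the equipment, so an error would not average out across infants. At a site with one type of scale, every case that depends on the item goes the same way. At stake is the site-level SGA applicability proportion, and with it the distribution over levels and the tabulated reasons why cases could not be classified.

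**Working it through.** **1. The plan's own precision figure.** Section 5.1.2 gives 97 cases for a proportion of 50% and a margin of 10 points. With n = 1.96² × p(1 − p) / d², p = 0.5 and d = 0.10:

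n = 3.8416 × 0.25 / 0.01 = 96.04, rounded up to 97.

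The figure reproduces. At the target of 100 cases the half-width is 1.96 × √(0.25/100) = 0.098, or 9.8 points.

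**2. Mapping graduations to answers and criteria.** The 50 g answer is taken first as 50 g or finer, which is the sense that LBW Level 2 needs, and then literally as 50 g or coarser.

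| Scale graduation | Answers a site could give | SGA 2A/2B/3A (<50 g) | LBW Level 2 (50 g or finer) |
|---|---|---|---|
| 1, 2 or 5 g | 50 g answer (read as or finer); Other | met | met |
| 10 g | 10 g answer | met | met |
| 20, 25 or 49 g | 50 g answer (read as or finer); Other | met | met |
| 50 g | 50 g answer (either reading); Other | not met | met |
| 100 g | 50 g answer (read as or coarser); Other | not met | not met |

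The 10 g answer decides the SGA criterion. The 50 g answer does not, because it covers scales on both sides of the SGA limit. Other decides nothing, because the value is not kept. No other item in the birth-weight form records resolution.

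**3. Either fixed rule misclassifies some scales.**

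- If the 50 g answer counts as meeting the SGA limit, cases weighed on a 50 g scale are wrongly classified.
- If it counts as not meeting the limit, cases weighed on a 20 to 49 g scale, or on a finer scale entered under that answer, are wrongly left out.

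**4. Whether another SGA level catches these cases.** Take an infant weighed directly in time, with dating that fits 2A, 2B or 3A.

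- Level 1 asks for 10 g resolution.
- Level 3B asks for weighing by difference with an adult.
- Level 4 starts from "Baby noted to be small, but no actual weight" and otherwise covers gestational age from infant examination alone, or a diagnosis from codes or chart without documented weight or gestational age.
- SGA has no SOP route.

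None of these takes the case.

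**5. Size at one site.** Let m be the number of such cases among 100 SGA cases. The two rules give applicability figures m points apart, with m anywhere from 0 to 100. From m = 10 the gap exceeds the 9.8-point half-width.

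**6. Secondary point on LBW.** An electronic scale finer than 10 g that is entered as Other fails LBW Levels 1 and 2 on this item. Level 3 lists dial, spring and colour-coded scales, so it does not take the case either. The SOP route may still do so.

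**The case against.** The strongest reply is that the effect may be empty in practice. The documents do not say how many sites use a scale that is not graduated to 10 g. The mapping lies in the classification tool, and the choice of answer may be settled in the completion guidelines or the manual of procedures; neither is shown. The one-off site questionnaire in section 4.8 covers the type of scale and might already hold the graduation. The value is a fixed property of the equipment, and site queries are already planned. All of this stands. It limits the size and makes the repair easy, but it does not let the form as written separate a 20 g from a 50 g scale.

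A reader might infer more than the documents support:

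- **That finer scales have no place on the form.** There are four answers, and the 50 g answer read as 50 g or finer admits 1 to 5 g scales. The weakness is that no answer is specific to them.
- **That LBW swings in the same way.** LBW Level 2 uses the cut-off that the form copies, and the SOP route can recover cases entered as Other. That Level 3 leaves out electronic scales comes from the definition, not from this item.
- **That the equipment comparison in section 5.3.2 is corrupted.** Section 4.8 says that such factors come from the separate site questionnaire. Graduation reaches that comparison only through the classified count.
- **That overall SGA applicability shifts by a stated number of points.** This would need the number of affected sites, their case counts and the share of cases with qualifying dating. None is given. The gap between two mapping rules is also a ceiling on ambiguity, not a bias estimate, since under either rule only some scales are misclassified.

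**Conclusion.** The point holds for SGA. The 50 g answer cannot decide the resolution criterion of Levels 2A, 2B and 3A, and Other is unspecified. The effect is confined to sites whose scale is not graduated to 10 g, and there to directly weighed cases with 2A, 2B or 3A dating. At such a site the applicability proportion can differ between mapping rules by the whole share of those cases. The number of affected sites is unknown and may be small or zero, so no overall figure can be given.

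This rests on two assumptions: that graduation is not recorded elsewhere in material not shown, and that LBW Level 2 means 50 g or finer. The LBW effect is secondary and conditional on the site's SOP. The change is worth making because the item feeds a primary numerator and costs little to correct.

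**What to change.** Replace the answer list in Scale item 2 by the graduation in grams, entered as a number once per scale. For cases already recorded, obtain it by a site query. Derive each criterion separately:

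- LBW Level 1 and SGA Level 1, graduation component: 10 g or finer;
- LBW Level 2, graduation component: 50 g or finer;
- SGA Levels 2A, 2B and 3A, resolution component: strictly below 50 g.

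State in the classification rules that 10 g is read as 10 g or finer, so that a better scale is not penalised. The other requirements of each level stay as they are.

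The cost is one changed CRF item, one query per site and a short derivation rule.

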### Maternal immunization

| QUESTION                                                                                  |                                                                                                                                                                                    | ANSWERS                                  |
|-------------------------------------------------------------------------------------------|------------------------------------------------------------------------------------------------------------------------------------------------------------------------------------|------------------------------------------|
| 1                                                                                         | What is the date of LMP ?
(if 'unknown', skip all questions on 30 days before LMP)                                                                                              | Please enter DDMMYYYY or unknown. |
| 2a                                                                                        | Did the mother receive any vaccination during pregnancy?
Please only answer 'no' if there is documented evidence of no immunization; else please answer 'unknown'.       | Yes
No
Unknown                     |
| 2b                                                                                        | Did the mother receive any vaccination in the 30 days before LMP? Please only answer 'no' if there is documented evidence of no immunization; else please answer 'unknown'. | Yes
No
Unknown                     |
| (If the answer to both question above is 'no' or 'unknown', end of questionnaire.) |                                                                                                                                                                                    |                                          |
| 3                                                                                         | How many vaccine doses were administered during pregnancy in total?                                                                                                                | 1
2
3
4
>4
Unknown        |
| Fill in the questions below for each dose administered during pregnancy                   |                                                                                                                                                                                    |                                          |

|                                                                          |                                                                                                                      |                                                                                                                                           |
|--------------------------------------------------------------------------|----------------------------------------------------------------------------------------------------------------------|-------------------------------------------------------------------------------------------------------------------------------------------|
| Dose during pregnancy                                      |                                                                                                                      |                                                                                                                                           |
| 4                                                                        | Against which disease was the mother immunized?                                                                      | Tetanus
Influenza
Pertussis
Other, please specify                                                                                |
| 5                                                                        | Was vaccination status obtained from medical records or reported by the mother?                                      | Medical records (e.g. ANC card, vaccination card, vaccine registry, etc.)
Reported by mother but no formal recording
Unknown        |
| 6                                                                        | What is the date of immunization of the pregnant woman?                                                              | Please enter DDMMYYYY or unknown.                                                                                                  |
| 7                                                                        | What is the time of immunization of the pregnant woman?                                                              | Please enter the time or unknown.                                                                                                  |
| 8                                                                        | Was the date recorded in medical records by health care worker who administered/witnessed administration of vaccine? | Yes
No
Unknown                                                                                                                      |
| 9                                                                        | What is the name of the vaccine?                                                                                     | Adacel
Boostrix
Daptacel
Infanrix
Kinrix
Pediatrix
Pentacel
Quadracel
Tenivac
Other, please specify
Unknown |
| 10                                                                       | What is the manufacturer?                                                                                            | GlaxoSmithKline
Sanofi Pasteur
Other, please specify
Unknown                                                                     |
| 11                                                                       | What is the lot number?                                                                                              | Please enter your answer in free text.                                                                                             |
| OPTION TO 'ADD DOSE DURING PREGNANCY' AND REPEAT QUESTIONS |                                                                                                                      |                                                                                                                                           |
| 12                                                                       | How many vaccine doses were administered in the 30 days before LMP?                                                  | Please select your answer from the list.
Fill in the questions below for each dose administered in the 30 days before LMP       |
| Dose 30 days before last LMP                               |                                                                                                                      |                                                                                                                                           |
| Same questions as above                                                  |                                                                                                                      |                                                                                                                                           |

**OPTION TO 'ADD DOSE 30 days before last LMP' AND  
REPEAT QUESTIONS**

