#### 4.7.8 Ascertainment of vaccine exposure

To assess whether sites are able to determine whether a vaccine had been administered during pregnancy or within 30 days prior to the last menstrual period (LMP). Maternal vaccination status for tetanus or any other vaccines administered during pregnancy will be ascertained for all mothers of identified cases with the health outcome of interest.

A mother who has any mention of maternal vaccination will be considered vaccinated (exposed). This could be a formal recording of vaccination or any other mention in the documents available to the sites.

A mother who has documented evidence of absence of maternal vaccination will be considered non-vaccinated (non-exposed).

Any mother without any indication will be considered to have exposure status 'unknown'.

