## **5.5 Handling of missing data**

Missing data will not be imputed, and the data will be analyzed as they are recorded in the eCRFs. Missing data will be tabulated and explored as described in the exploratory objectives.

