## **Maternal immunization**

### Level 1 of diagnostic certainty

1. Woman confirmed as pregnant by positive pregnancy test or ultrasound confirmation

AND

2. Date/time of immunization of pregnant woman recorded in medical records by health care worker who administered/witnessed administration of vaccine

AND

3. Details of vaccine, including lot number, date of immunization

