### Level 2 of diagnostic certainty

1. Woman confirmed as pregnant by cessation of menstrual period and gravid uterus

AND

2. Date (at least month and year) of immunization of pregnant woman recorded in medical records by health care worker who administered/witnessed administration of vaccine

AND

3. Details of disease against which vaccinated

Level 3 of diagnostic certainty

1. Woman/medical attendant reports pregnancy AND

2. Woman reports receipt of vaccination during pregnancy, but no formal recording of immunization available.

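### The dose form has no coded 'Unknown' for the disease vaccinated against, so an unmet GAIA Level 2 criterion may be recorded as met and maternal-immunisation applicability may be biased upward

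*Protocol*

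**What the plan says.** **The form.** In Annex V, Maternal immunization, item 4 asks "Against which disease was the mother immunized" and its full answer list is "Tetanus Influenza Pertussis Other, please specify". Items 5 to 10 of the same block (source, date, time, who recorded the date, vaccine name, manufacturer) all accept an unknown answer. Item 6, for example, asks "What is the date of immunization of the pregnant woman" and takes a date or unknown. Item 11, the lot number, carries only the instruction "Please enter your answer in free text". The block for doses in the 30 days before the last menstrual period repeats the same questions.

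**The definition.** In Annex III, the third criterion of Level 2 is "Details of disease against which vaccinated". The third criterion of Level 1 is "Details of vaccine, including lot number, date of immunization". Level 3 needs neither item, but it covers only vaccination reported by the woman with no formal record.

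**Who is counted.** Section 4.7.8 states: "A mother who has any mention of maternal vaccination will be considered vaccinated (exposed". Section 5.2.2.2 then measures applicability, as part of primary objective 2, as vaccinated mothers who can be classified divided by vaccinated mothers identified.

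**Handling.** Classification is done by an automated tool (section 4.10). Section 8.1 provides for eCRF feedback on missing entries. Section 5.5 rules out imputation and says "the data will be analyzed as they are recorded in the eCRFs".

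**The concern.** The form allows for the vaccine name, manufacturer, date, time and even the source being unknown, but not the disease. The disease is the element on which Level 2 turns for a dated record without a lot number. The study is meant to find out whether sites can record such elements, and for this one the form has no coded way to say that they could not.

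The exposure rule makes such records possible: a note that a vaccine was given, without saying against what, is enough to make the mother exposed. A site facing item 4 for that record, with a prompt if it is left empty, may tick the vaccine it gives routinely. The tool would then see the criterion as met. The resulting error in the primary proportion could only be upward. It could not be seen centrally either, because section 8.3 keeps source documents within the site.

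**Working it through.** The protocol states no figure on this point, so there is none to reproduce. The check sets the form against the definition and then bounds the effect.

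**Step 1. Which answer lists lack an unknown?** Items 5 to 10 accept it. Item 4 does not. Item 11 is open text with no coded non-value.

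**Step 2. Which criteria do they feed?** Item 4 feeds Level 2, criterion 3. Item 11 feeds Level 1, criterion 3. The date criterion of Level 2 is fed by items 6 and 8, both of which can be answered as unknown.

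**Step 3. Follow one record.** Take a dose formally recorded and dated by the vaccinating worker, with no disease named, no vaccine name from which to infer it and no lot number. Assume the pregnancy criterion is met.

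| Level | Outcome if recorded truthfully | Outcome if a disease is ticked at item 4 |
|---|---|---|
| 1 | fails: no lot number | fails: no lot number |
| 2 | fails: no disease | can be credited |
| 3 | fails: a formal record exists | not needed |
| Result | unclassified | Level 2 |

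Mother-reported doses can reach Level 3 without a disease, so they are unaffected. A dated dose with full vaccine details and lot number can meet Level 1 without item 4, so it is unaffected too.

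**Step 4. Size.** Let A be true applicability, u the share of vaccinated mothers whose record is of the kind in step 3, and f the share of those for whom a named disease is ticked. Then

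recorded applicability = A + u × f.

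The documents give none of A, u or f. The values below are assumptions.

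| A | u | f = 0 | f = 0.5 | f = 1 |
|---|---|---|---|---|
| 50% | 2% | 50% | 51% | 52% |
| 50% | 5% | 50% | 52.5% | 55% |
| 50% | 10% | 50% | 55% | 60% |
| 80% | 2% | 80% | 81% | 82% |
| 80% | 5% | 80% | 82.5% | 85% |
| 80% | 10% | 80% | 85% | 90% |

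The excess is u × f whatever A is: 0 to 2, 0 to 5 and 0 to 10 percentage points for the three values of u. With a coded *Unknown* that counts as not met, and used where the source names no disease, f is 0 and the form adds no bias.

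**Step 5. Lot number.** If text such as 'not known' in item 11 were read as a lot number, a dose that meets Level 2 could be moved to Level 1. That changes the split by level (secondary outcome, section 5.3.1.2). It adds 0 points to any-level applicability where Level 2 is already met. How the tool reads such text is not shown in the protocol.

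**The case against.** The strongest reply is that nothing forces a false answer. Section 8.1 describes feedback on missing data, which is a prompt, and the protocol nowhere makes item 4 mandatory. A site can leave it blank or write 'unknown' under the specified-other option, and section 5.5 says missing data are tabulated. Section 4.8 requires entries to rest on source documents, so ticking a disease that the source does not name would breach the protocol. Completion guidelines, a procedures manual, manual data review and queries are also planned. The affected group is narrow, because the disease, an informative vaccine name and the lot number must all be absent from a formally dated record.

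Most of this stands, and it rules out several stronger readings that a reader might infer:

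- *That criterion 3 of Level 2 can never be recorded as unmet.* A blank or a text entry under the other option can do so.
- *That applicability is shown to be overstated.* This needs both such records and wrong ticks, and the documents give no frequency for either.
- *That the missing lot-number code inflates applicability in the same way.* The lot number belongs to Level 1. Where Level 2 is met it affects only the split between levels.
- *That the gap hides entries from the missing-element tables of section 5.4.* Those tables are specified for health outcomes and cases, while vaccination is handled separately as an exposure.
- *That allowing several diseases per dose would matter here.* One named disease already meets the criterion, so neither the level nor applicability would change.

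The reply does not remove the gap itself. The protocol does not say how a blank or a typed non-value in item 4 is classified, and a wrong tick looks like a valid answer to anyone outside the site.

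**Conclusion.** The point holds as a defect in the instrument behind part of a primary outcome. An unmet Level 2 criterion 3 has no coded answer, and some doses may be credited as Level 2 when they should be unclassified. Any bias in maternal-immunisation applicability from a wrongly ticked disease is upward and equals u × f. On assumed u of 2% to 10% the ceiling is 2 to 10 percentage points, reached only if every affected record is given a named disease. The floor is zero. These figures rest on assumed inputs and are not estimates of what happened. The lot-number gap is a lesser matter, confined to the Level 1/Level 2 split where Level 2 is met. The correction is worth making because it is specific and cheap, and because the error cannot be found centrally once entered.

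**What to change.** - Add a coded *Unknown / not recorded* answer to item 4 and to item 11, in both the pregnancy and the pre-LMP dose blocks.
- State that this answer, a blank, or a free-text non-value counts as criterion not met: item 4 for Level 2, item 11 for Level 1.
- For records already entered, recode free-text non-values as missing and ask sites to check item 4 against the source. The sites have to do this themselves, since the source is not visible outside them.

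The cost is two answer options, one classification rule, a recode and some site queries. Reported applicability may come out slightly lower.
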